### Trial aims and hypotheses

We plan to examine SAIA-Naloxone’s impact in SSPs compared to an implementation-as-usual (IAU) condition across three aims and several related hypotheses.

#### Aim 1

Our first aim is to test the effectiveness of SAIA-Naloxone on improving naloxone distribution within SSPs. We hypothesize that compared with SSPs receiving IAU, SSPs receiving SAIA-Naloxone will significantly increase the number of people receiving naloxone and number of naloxone doses distributed during the 12-month active period. Further, we hypothesize that SSPs receiving SAIA-Naloxone will significantly increase the number of people receiving naloxone in the 6 months after the active period (the sustainment period) compared with SSPs receiving IAU.

#### Aim 2

Our second aim will test the effectiveness of SAIA-Naloxone on improving naloxone distribution at SSPs to BIPOC and other key subgroups. We hypothesize that SAIA-Naloxone will significantly increase the number of BIPOC and women receiving naloxone from them during the 12 months active period and during the 6-month sustainment period. To test this hypothesis, we anticipate utilizing a subset of SSPs that report disaggregated outcome data based on participant level demographics like race, ethnicity, and gender.

#### Aim 3

Our third aim will estimate the cost and cost-effectiveness of SAIA-Naloxone on improving equitable access to naloxone at SSPs, relative to IAU. We hypothesize that, relative to IAU, SAIA-Naloxone will be cost-effective at increasing the number of people receiving naloxone from SSPs. We also hypothesize that, relative to IAU, SAIA-Naloxone will be cost-effective at increasing the number of BIPOC receiving naloxone from SSPs.

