### Data analysis and power calculation

Before model fitting, we will assess whether there is significant variation across the three potential levels of aggregation for each outcome: (1) within-SSP level (repeated measures over time), (2) between-SSP level, and (3) county level. We will also examine the functional form of changes over time in outcomes. We assume that piecewise linear (i.e., linear change during the 3-month lead-in period, post-implementation linear change from baseline through 18 months, and a period of treatment effect “deterioration” (if any) between 12 and 18 months) will be the predominant functional form, though with this large number of assessments, nonlinear forms may be necessary [56–58]. We will estimate a random intercept (*π*_*0is*_), which is the estimated (conditional) mean value of the outcome at time = 0 (e.g., lead-in baseline), and two random slopes (*π*_*1is,*_* π*_*2is*_): (1) the estimated per-year change in Y from the lead-in phase through 18 months; and (2) the “deterioration” phase, capturing how much reduction there is in change over the last year, if any, for the SAIA-Naloxone condition.

Level 2 will examine the between-SSP level effects. The key predictor included in *X*_*qis*_ is a 0/1 dummy indicator indicating whether SSP *i* was in the SAIA-Naloxone condition or IAU. *β*_*1s*_ will capture the average change over time in naloxone distribution (and other outcomes), which (1) should not be significantly different from zero during the lead-in period and (2) will vary by SAIA-Naloxone and IAU after implementation (by virtue of the SAIA-Naloxone × time period 1 interaction). *β*_*0s*_ will capture the conditional mean level of naloxone distribution, which, if it varies by implementation condition, would capture a mean shift in our study outcomes. *β*_*2s*_ will capture the change over time in naloxone distribution during the second year; if it interacts with the SAIA-Naloxone indicator, it will capture slope differences over time beyond 1 year between SAIA-Naloxone and the IAU condition, with Year 1 gains maintained if this parameter estimate is nonsignificant.

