Level 3 will capture county-level variability in intercepts and, if necessary, slopes over time. As mentioned previously, our Aim 2 analysis will use the subset of SSPs that report outcome data disaggregated by race, ethnicity, and gender. For both Aims 1 and 2, we will reject the null hypothesis (i.e., there are no differences between SAIA-Naloxone and IAU SSPs regarding the test statistics described above) if *p*-values are equal to or less than an alpha coefficient of 0.05.

We structured a Monte Carlo power analysis [59] using the parameters from our pilot. For Aim 1, we structured a population model based on the number of weekly data submissions from SSPs) with a binary predictor structured to have the following effects, using the lead-in period standard deviation across 1 year in the pilot (15.09) as the denominator for the effect size. The mean shift in post-implementation outcomes was 22.76 additional people served under SAIA-Naloxone, yielding a Cohen’s *d* of 1.50. The per-week increase in number served under SAIA-Naloxone was 1.29, reaching a longitudinal Cohen’s *d* effect size [60, 61] of 1.0 by 11 weeks. We generated 250 synthetic samples of *N* = 32 and analyzed the samples in Mplus while imposing the random effect structure from pilot estimates and a county-level intraclass correlation of 0.05. Specific to Aims 1 hypotheses that pertain to the active 12-month phase, we will have at least 80% power to detect a post-implementation mean shift and differences in slopes over time. Specific to Aims 1 hypothesis that pertain to the sustainment phase, detecting treatment effect deterioration from 12 to 18 months for 80% power requires deterioration equivalent to a Cohen’s *d* of 0.48. The extremely large number of repeated measures offsets the sample size of 32 with regard to statistical power to detect slope differences [62].

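### The sustainment rule treats a nonsignificant slope term as proof that gains were kept, and it does not test the 6-month hypothesis stated under Aim 1

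*Protocol article*

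**What the plan says.** Under Aim 1 (Trial aims and hypotheses), the sustainment hypothesis is a between-arm superiority claim: SAIA-Naloxone programs "will significantly increase the number of people receiving naloxone in the 6 months after the active period (the sustainment period) compared with SSPs receiving IAU".

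Data analysis and power calculation sets out a piecewise growth model with a random intercept and two random slopes. The first slope is "the estimated per-year change in Y from the lead-in phase through 18 months". The second is a deterioration term, "capturing how much reduction there is in change over the last year, if any, for the SAIA-Naloxone condition". Two sentences later the corresponding level-2 coefficient is described differently: if it interacts with arm, "it will capture slope differences over time beyond 1 year between SAIA-Naloxone and the IAU condition". The decision rule follows directly: "with Year 1 gains maintained if this parameter estimate is nonsignificant".

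The only power statement tied to the sustainment hypothesis is that "detecting treatment effect deterioration from 12 to 18 months for 80% power requires deterioration equivalent to" a Cohen's d of 0.48. Alpha is 0.05. Table 2 places the sustainment phase in study months 16–21, which are months 13–18 after randomisation.

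**The concern.** Three things are at issue, of unequal strength.

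- **Decision rule.** Failing to find a significant slope term is taken as evidence that nothing was lost. Noisier data make that outcome more likely, and the article itself expects data submissions to fall from 98% at 12 months to 92% at 18 months.
- **Hypothesis and test.** Aim 1 succeeds by rejecting a null about the arm difference in the last 6 months. The rule succeeds by failing to reject a null about a slope. An advantage over usual implementation can survive some deterioration, and an absence of detected deterioration does not show that an advantage exists.
- **Meaning of the second slope.** The two descriptions lead to different codings, and a plateau gets a different verdict under each.

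At stake is the trial's statement on whether the strategy's effect lasts after the facilitator leaves.

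**Working it through.** **Inputs**, all from Data analysis and power calculation unless noted: d = 0.48 at 80% power; alpha 0.05 (sidedness not stated, two-sided assumed); standard deviation 15.09; mean shift 22.76 people; pilot slope 1.29 people per week; 16 programs per arm (Trial aims and hypotheses).

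**Step 1. The plan's own figures.** The mean-shift effect size reproduces: 22.76 / 15.09 = 1.51, against 1.50 stated. The d = 0.48 cannot be reproduced or refuted, because it comes from a simulation using pilot random-effect variances that the article does not give. It is taken as given below.

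**Step 2. Implied precision.** Read d = 0.48 as the total loss over the 6 months, with a separate second-period slope. Then

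SE = 0.48 / (1.960 + 0.842) = 0.171 on the d scale, or 0.171 × 15.09 = 2.6 people.

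**Step 3. Chance that the rule says maintained despite a real loss.** Probability = 1 − Φ(d/0.171 − 1.96); the opposite tail is negligible.

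| True loss d | People (d × 15.09) | Share of the 22.76 shift | Called maintained |
|---|---|---|---|
| 0.24 | 3.6 | 16% | 71% |
| 0.30 | 4.5 | 20% | 58% |
| 0.36 | 5.4 | 24% | 44% |
| 0.48 | 7.2 | 32% | 20% |

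A t distribution with 30 degrees of freedom gives the same values to within 0.1 percentage point.

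**Step 4. Hypothesis against test.** Aim 1 concerns how many people receive naloxone, SAIA-Naloxone against usual implementation, over 6 months. Under either coding the second-slope interaction is a rate, not that difference. The article names no contrast for those 6 months and gives no power for one.

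**Step 5. A plateau under the two codings.** Let the arm difference grow by b per week up to month 12 and then stay exactly where it is.

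- *First slope running through 18 months, second slope as the reduction in change:* after month 12 the weekly change is b + β₂ = 0, so β₂ = −b. Fully kept gains give a negative term, which may be significant and be read as deterioration. A term of zero would mean that the gap keeps widening at its Year 1 rate.
- *Separate slope after month 12:* β₂ = 0, and the plateau is not flagged.

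A noiseless piecewise fit with b = 1.29 confirms this: β₂ = −1.29 under the first coding and 0 under the second.

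**The case against.** The strongest objection is that the two kinds of error cannot be charged to one rule. The percentages in Step 3 need a separate slope (or a flat Year 1 slope); the plateau problem needs the change-of-slope coding. This stands. A reader might infer that the rule errs in both directions at once, but no single reading of the model produces both.

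A reader might also put a large number on the plateau error: 1.29 × 26 / 15.09 = 2.22, far above 0.48. The article does not support that. It uses 1.29 per week only to say when d = 1.0 is reached, at about 11 weeks; carrying the slope to month 12 means 1.29 × 52 = 67 people, which it never asserts. It also allows for nonlinear forms. The plateau point therefore stays conditional and without a size.

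It can be said that the test is not weak, since 0.48 is about one third of the assumed mean shift. That is fair. The fault lies in the inference drawn from nonsignificance, not in a demonstrated shortage of power.

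The arm difference over months 13–18 after randomisation is a combination of parameters that the planned model already estimates, and an analysis plan not shown here might name it. So a reader should not infer that the hypothesis is untestable. But the article does more than leave a detail open: it states a different rule and ties its sustainment power to that rule.

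Finally, the references to the last year and the second year are minor, because the same section also gives the period as 12 to 18 months.

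**Conclusion.** Wrong as written. Two parts hold outright: nonsignificance is the stated criterion for maintenance, and the rule and its power statement do not address the Aim 1 sustainment hypothesis. The slope-coding part holds conditionally: the section supports two definitions, and only one of them turns a plateau into apparent deterioration.

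The size is that a true loss of d = 0.24 is called maintained about 71% of the time and a loss of d = 0.48 about 20%. This rests on two-sided alpha 0.05, a normal approximation, the same standard error at every loss, separate-slope coding, and d = 0.48 meaning total loss over the 6 months. The active-phase hypotheses are not affected, and nothing here shows that d = 0.48 is itself mistaken.

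**What to change.** 1. Make the sustainment test the between-arm contrast in people receiving naloxone over months 13–18 after randomisation, taken from the planned model, and state power for it. As a rough guide, a simple comparison of 16 with 16 programs, assuming SD 15.09 and power = Φ(d/√(2/16) − 1.96), gives 99% if the full d = 1.51 remains, 83% if d = 1.03 remains (a loss of 0.48), and 57% if half remains. The planned model needs its own rerun.
2. Fix one phase-specific slope coding and describe the second slope the same way throughout.
3. Report the change in the arm difference from the end of the active phase with a 95% confidence interval. Claim maintenance only if the interval excludes a pre-set, justified loss; otherwise report the result as inconclusive. Half the effect is too lenient as a default margin: with a margin of 0.75 and SE 0.171, Φ((0.75 − 0.24)/0.171 − 1.96) is about 85%, so a loss of d = 0.24 would be called maintained more often than under the present rule (71%).
4. Align the wording on the last or second year with the 6-month period.

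The cost is analysis wording and one power rerun, to be settled before outcomes are seen. The downside is that some results will be inconclusive. With no true loss and SE 0.171, a margin of d = 0.48 would be met 80% of the time and a margin of a quarter of the mean shift (d = 0.38) about 60%. Both margins are illustrations, since the article gives none.

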## Discussion

This trial represents several important advancements within implementation research. Since the initial SAIA trial to improve prevention services for mother-to-child HIV transmission in Kenya, Mozambique, and Côte d’Ivoire in 2014, the strategy has been adapted several times for the purposes of improving hypertension, mental health, and adult and pediatric HIV care systems across the region [23–26]. To our knowledge, this trial will be one of the first randomized trials of SAIA in the United States and among SSPs, and the first focused on improving the naloxone cascade and on equity-centered outcomes.

The study’s U.S. focus comes at a critical moment, as the country has experienced the highest levels of opioid overdose mortality in its history [2, 3, 66]. Racial disparities are present within the epidemic with BIPOC experiencing some of the least favorable outcomes [3, 4]. In response to the crisis, lawmakers at the federal level and in every state have enacted some type of naloxone access legislation to improve distribution of the lifesaving treatment [67–71]. Despite these legal efforts, naloxone distribution remains insufficient against the backdrop of persistently increasing opioid-related fatalities [5]. To combat the epidemic and the disparities within, researchers have called for multifaceted strategies focused on community-based organizations that address major barriers—such as structural racism—to improve naloxone distribution [30, 72–74]. SAIA-Naloxone represents an attentive response to these calls given its focus on working within SSPs and toward equity-focused outcomes. SSPs are often community-based programs that PWID trust to provide quality health care amidst systems that criminalize and stigmatize substance use [29, 75]. SAIA-Naloxone’s multifaceted and multilevel strategies also respond to the complex and unique needs of different SSPs throughout California. If successful, SSPs may utilize recently released federal and state funds focused on curbing the epidemic to adopt SAIA-Naloxone as a means of improving naloxone distribution.

This trial also takes a pragmatic and theory-informed approach to specifying SAIA-Naloxone and assessing its fidelity. Our approach combines Proctor et al.’s (2017) strategy specification recommendations with Carroll et al.’s (2007) conceptual framework of implementation fidelity [33, 39]. In doing so, we hope to clearly report the strategy’s activities as well as assess the extent to which they were carried out as intended. Combining structured specification and fidelity assessment might improve our understanding of not only how the strategy works but also of the likelihood that impacts on outcomes are due to the strategy itself and not to other factors (i.e., assessment of a type III research error). Fidelity results may additionally highlight facets of the strategy’s implementation that future applications could harness or improve.

The current study builds upon existing evidence for the SAIA strategy [23–26] as well as our own pilot work that brought SAIA into SSPs [28]. If successful, SAIA-Naloxone may represent a pragmatic and scalable systems approach to combating the opioid overdose mortality crisis and the disparities within.

## Data Availability

N/A.

## Abbreviations

BIPOC: Black, Indigenous, and people of color
CAT: Cascade analysis tool
CDPH: California Department of Public Health
CEAC: Cost-effectiveness acceptability curve
CHRI: California Harm Reduction Initiative
CQI: Continuous quality improvement
IAU: Implementation as usual
ICER: Incremental cost-effectiveness ratio
NCAT: Naloxone cascade analysis tool
PWID: People who inject drugs
SAIA: Systems Analysis and Improve Approach
SASCAP: Substance Abuse Services Cost Analysis Program
SSP: Syringe service program
